## Abstract

**Introduction::**

Female farmers commonly experience musculoskeletal pain in the back, knee, and shoulder. Despite their obvious advantages in reducing musculoskeletal pain, face-to-face exercise programs are limited by geographical and physical barriers. Thus, we decided to introduce eHealth technology to farmers’ musculoskeletal health care. Using a mobile application (app), we aim to provide a tailored self-exercise program for shoulder, knee, and back pain in female farmers in rural areas after a musculoskeletal health check-up.

**Methods::**

This study is planned as 2 randomized control studies (MObile Delivered self-Exercise [MODE] phase I and phase II). We plan to recruit 200 female farmers aged 41 to 70 years. Initially, the shoulders, knees, and low back will be evaluated to provide individualized exercise programs. In MODE-I (single-blinded: evaluator), the subjects will be randomly allocated to experimental (n = 100) and control (n = 100) groups using a computer-generated sequence. Both groups will perform a 3-month self-exercise using a smartphone app or physical education data (booklets), respectively. Outcomes including exercise completion will be assessed at 3 months. In MODE-II, after subject random allocation, the experimental and control groups will perform exercise using a smartphone app with and without real-time feedback, respectively. Every 3 months, the level of the exercise program will be evaluated and the difficulty level will be adapted accordingly. After MODE-II is completed, all subjects will undergo close-out assessment.

**Discussion::**

This will be the first attempt to compare methods using booklets and apps to identify effective ways of providing personalized self-exercise programs according to musculoskeletal health stages by evaluating female farmers (MODE-I). This will help clarify whether the mobile app is effective for self-exercise compared to a conventional booklet. The MODE-II study will help to assess the effect of providing feedback through the mobile app. Finally, we will evaluate musculoskeletal health according to the degree of participation over 12 months to confirm the effect of self-exercise. Our study should aid in managing musculoskeletal health for farmers living in rural areas and help promote health in the “untact” era.

**Trial registration::**

Clinical Research Information Service of the Korean National Institutes of Health (KCT0005245). Registered July 17, 2020.

## Introduction

1

Farmers commonly experience musculoskeletal pain in the back, knee, and shoulder, and female farmers are particularly more vulnerable to musculoskeletal disorders than men.^[1]^ Therefore, the Ministry of Agriculture, Food, and Rural Affairs in Korea plans to conduct musculoskeletal health checks for female farmers in the near future. The government-led health examinations primarily aim to identify people with musculoskeletal disorders.

Musculoskeletal disorders are very common and tend to worsen over time without proper managements. Therefore, a comprehensive management for preventing diseases and maintaining function as well as symptom improvement is considerably important. Exercise programs are very effective in reducing musculoskeletal pain.^[2]^ To date, exercise programs have been conducted face-to-face. Despite their obvious advantages in reducing musculoskeletal pain, face-to-face education and exercise programs are limited in their overall implementation,^[3]^ and it is expected that there will be limitations in conducting face-to-face exercise programs, which are suitable for candidates at the national level.

A health check-up project will be launched to evaluate the musculoskeletal health of female farmers. Rural areas have a large area and a low population density. In areas with low population densities, human resource limitations are expected to be maintained in community-based centers of exercise. To overcome geographical and physical barriers, we decided to introduce eHealth technology to farmers’ musculoskeletal health care.

By developing a self-exercise provided through a mobile application (app), we can provide female farmers living in rural areas with a tailored exercise program for shoulder, knee, and back pain after a baseline assessment. The mobile app is developed without feedback (feedback-) and with real-time feedback (feedback+). In phase I of this study, the effect of the feedback- app will be compared with the classic booklet with respect to self-exercise, and in phase II, the effects of the feedback+ and feedback- apps on self-exercise will be compared.

Our hypotheses are that the feedback- app-delivered self-exercise program will result in higher completion rates of 3-month self-exercise compared to the booklet-delivered self-exercise program, and that the feedback+ app-delivered exercise program will result in higher completion rates of 9-month self-exercise compared to the feedback- app-delivered exercise program.

## Methods/design

2

### Study design

2.1

This study is planned as 2 randomized control trials. The phase I and II trials of the MObile Delivered self-Exercise (MODE) study will be randomized, prospective, single-blind (evaluator), and include active comparator controlled trials to test the effect of an app-delivered self-exercise program on the facilitation of self-exercise, musculoskeletal pain, and health behavior in female farmers aged 41 to 70 years. This study has been approved and conforms to the Declaration of Helsinki. This study was designed according to the CONsolidated Standards Of Reporting Trials (CONSORT) statement^[4]^ and is reported according to the Standard Protocol Items: Recommendations for Interventional Trials (SPIRIT) statement.^[5]^ The schedule of trial enrolment and assessments is shown in Table 1. The trial flow chart is shown in Figure 1.

**Table 1 T1:** The schedule of trial enrolment and assessments.

	Study Period								
Assessment	Enrolment	Allocation	MODE I		MODE II				Close-out
Time point	-t_1_	0	t_1_	t_2_	t_3_	t_4_	t_5_	t_5_	t_6_
Enrolment:									
Eligibility screen	X								
Informed consent	X								
Allocation		X			X				
Interventions:									
Tool usage education			X		X				
App-delivered exercise group				X		X	X	X	
Booklet-delivered exercise group				X					
Assessment:									
Demographics		X							X
Agricultural information		X							X
Medical history		X							
Current medication		X							X
Smartphone usability		X							
Participation in self-exercise				X		X	X	X	
Satisfaction with self-exercise				X		X	X	X	
Depression (PHQ-9)		X		X					X
Shoulder disability (SPADI)		X		X					X
Hip and knee disability (WOMAC)		X		X					X
Back disability (ODI)		X		X					X
Vital sign		X							X
Anthropometric measurement		X		X					X
Bioimpedance analysis		X		X					X
x-Ray		X							X
Bone density DEXA		X							X
Trunk extension strength		X							X
Musculoskeletal physical examination		X							X
Hand grip strength		X							X
Balance test (TUG and BBS)		X							X
Pulmonary function test		X							X
Blood chemistry		X							X

**Figure 1 F1:**
[figure not shown]
Consolidated Standards of Reporting Trials (CONSORT) flow diagram including participants’ recruitment, eligibility, screening, randomization, and outcome assessments of MODE phase I and II.

### Trial status

2.2

The enrolment of participants is currently ongoing at the time of submission study. Recruitment began on July 7, 2020.

### Participants

2.3

The subjects will be recruited through women's farmers’ organizations in connection with the Gangwondo Agricultural Research and Extension Services. Subjects’ eligibility for inclusion will be determined during the screening process. If eligible, subjects will be assigned to 1 of the 2 groups, experimental or control groups, according to the randomization method. Personal data will be numerically coded and stored in a separate database. All study information will be provided to all participants.

### Inclusion criteria

2.4

The inclusion criteria are as follows: women who cultivate crops on farmland exceeding 1000 m^2^ or engage in agriculture for ≥90 days in 1 year; women who cultivate crops by installing facilities >330 m^2^, such as a fixed greenhouses, mushroom barns, or vinyl-greenhouses; women who breed ≥2 large livestock, ≥10 medium livestock, ≥100 small livestock, ≥1000 birds or ≥10 beehives, or who are engaged in the livestock industry for ≥120 days or more; women with annual sales of agricultural products exceeding 1.2 million won accruing from agricultural management; and smartphone users.

### Exclusion criteria

2.5

The exclusion criteria are as follows: women with trauma and surgical history of shoulders, knees, and low back within the last 6 months; subjects with systemic diseases that cause chronic back pain (eg, cancer, infection, and so on); those whose limbs (part or whole) are amputated and in those in whom examining their body composition is difficult; those with low body weight (≤40 kg); and pregnant women.

### Study interventions

2.7

#### MODE-I

2.7.1

Participants who meet the inclusion criteria will be randomized to the app or booklet. Both groups will receive an individual-tailored exercise program via the mobile app or booklet (Fig. 2).

**Figure 2 F2:**
[figure not shown]
Mobile app (A) and booklet (B) for the self-exercise program.

##### Individual-tailored exercise program

2.7.1.1

Initially, the shoulders, knees, and low back will be evaluated, and musculoskeletal health status for each region will be divided into 3 levels to provide individualized exercise programs. Musculoskeletal function assessment includes self-administered questionnaires (Shoulder Pain and Disability Index [SPADI], Western Ontario and McMaster Universities [WOMAC], and Oswestry Disability Index [ODI]) and are categorized as mild and severe groups for each part (shoulder, knee, and back). The exercise for each part is programmed for 3 months with 4 levels of difficulty (from level 1 with the lowest difficulty to level 4 with the highest difficulty) (Table 2). Each exercise level for shoulder, knee, and back will be prescribed differently depending on their musculoskeletal health status, respectively. Level 1 is prescribed for high risk and level 2 for moderate risk for MODE-I (Table 3).

**Table 2 T2:** Levels of exercise for the shoulder, knee, and low back.

	Shoulder	Knee	Low back
Level ½	Trunk and shoulder stretchingIsometric shoulder forward/abduction/external-rotation exerciseScapular stabilizing exercise	Quadriceps exerciseStep up	Bird-dog easyAbdominal exercise easySide-bridging exercise easy
Level 3	Isotonic exercise using elastic band(s)	Lunge	Supine bridging
Level 4	Isotonic diagonal exercise	Balance	Plank

**Table 3 T3:** Overview of the content of the self-exercise plans.

Risk levels	MODE phase I	MODE phase II (II-1)	MODE phase II (II-2)	MODE phase II (II-3)
Mild	Level 2	Level 2 or 3	Level 2, 3, or 4	Level 2, 3, or 4
High	Level 1	Level 1 or 2	Level 1, 2, or 3	Level 1, 2, 3, or 4

The exercise characteristics include the following: type: 1 stretching and 1 strengthening exercises for the shoulder, knee, and back (total 6 exercises per day); frequency: 3 times per week; duration: 20 min/day; and intensity: 2 levels (Table 2).

##### Experimental group

2.7.1.2

The experimental group (app-delivered exercise group) will perform 3-month self-exercise using a smartphone app.

##### Active control group

2.7.1.3

Subjects belonging to the active control group (booklet-delivered exercise group) will perform 3-month self-exercise provided by booklets.

#### MODE-II

2.7.2

##### Individual-tailored exercise program

2.7.2.1

The following outcomes, including exercise completion, will be assessed at 3 months, and the subjects will be randomly allocated to MODE-II groups. The difficulty level of the exercise program will be adjusted individually at the time of allocation to MODE-II. Every 3 months, the level and the level of the exercise program will be evaluated and the level of difficulty will be changed (Table 3).

##### Experimental group

2.7.2.2

In MODE-II, the experimental group (feedback+ app group) will exercise using a smartphone app that adds feedback to the subjects (Table 4).

**Table 4 T4:** Real-time feedback provided by the mobile application.

Types of feedback	Schedule reminder	Real-time feedback	Get badge
Explanation	Reminder of the day's exercise schedule	Notification of the progress of exercise and comparison with the exercise yesterday	Award badge for successive workouts
Example	1) “Today is a workout day.”2) “An exercise reservation is made at 7 pm today.”	1) After 10 minutes of stopping the exercise video“You achieved 50% of today's workout. Try a little harder”“You have achieved 100% of today's workout. Awesome! Keep exercising like you have just been doing”2) When the specified (alarm) exercise time is over 30 min“You would have achieved the exercise goal if you…”“What are you doing? Start again with a new resolution and work harder”	1) Achievement of workouts (1, 3, 5, 7, 10, 15, 20, 25, 30, and 100 workouts)2) Continuous recording (2, 3, 4, 5, 6, and 7 wk; 2, 3, 4, 5, 6, 7, 8, 9, 10, and 11 mo; and 1 y)3) Weekly exercise (3 times a wk, 2 times a wk, 4 times a wk twice, 5 times a wk, 6 times a wk, 7 times a wk)4) By exercise time (early bird/owl)

##### Active control group

2.7.2.3

Subjects belonging to the active control group will perform self-exercise using a smartphone app without the feedback function (feedback- app group).

### Assessment

2.8

The primary and secondary outcomes will be assessed at baseline, 3 months, 6 months, 9 months, 12 months, and postintervention (Table 1). All participants will be requested to complete follow-up assessments, except for those who withdraw or are withdrawn from the study. Those who withdraw will be asked to identify reasons for withdrawal. After the completion of the MODE-II exercise, all subjects will undergo close-out assessment.

### Baseline assessment at baseline and close-out

2.9

Blood pressure, pulse rate, and waist circumference will be measured. Bone density will be assessed using dual-energy x-ray absorptiometry. Respiratory evaluations including chest radiography and pulmonary function test will be conducted, in addition to ophthalmic examination including tonometry and funduscopy. Laboratory tests will be conducted including total cholesterol, low density lipoprotein-cholesterol, high-density lipoprotein-cholesterol, triglyceride, blood urea nitrogen, creatinine, aspartate aminotransferase, alanine aminotransferase, fasting glucose, and hemoglobin A1c.

### Primary outcomes

2.10

The completion rate of the self-exercise program at the completion of MODE-I (3 months) and MODE-II (12 months) will be assessed with phone call assessment. Participants will be asked about the self-exercise as follows: “Did you exercise using the app (or booklet) we provided in the past 3 months?”

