#### Maintaining self-exercise with MODE-II

2.11.1

Maintenance rate of self-exercise program every 3 months during MODE-II (6 and 9 months) will be assessed with phone call assessment. Exercise time using the app will be assessed and compared between the experimental and control groups in MODE-II.

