### Sample size calculation

2.15

We assumed that the exercise completion rate with 3-month self-exercise using the smartphone app would be 60%; we expected that the completion rate with 3-month self-exercise by providing physical education data (booklets) would be 40%. With these assumptions, we estimated that we would need to enroll 200 participants for MODE phase I with an alpha level of 0.05 and a beta level of 0.20. With 20% of phase I subjects expected to drop out, 160 subjects would be needed for MODE phase II.

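### The MODE-II hypothesis is about nine months of self-exercise, but its primary outcome asks only about the last three

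*Protocol article*

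**What the plan says.** The Introduction states the MODE-II hypothesis: the feedback+ app "will result in higher completion rates of 9-month self-exercise compared to the feedback- app-delivered exercise program".

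Section 2.10 (Primary outcomes) sets the time points and the mode of collection. The completion rate "at the completion of MODE-I (3 months) and MODE-II (12 months) will be assessed with phone call assessment". It gives one question: "Did you exercise using the app (or booklet) we provided in the past 3 months".

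Section 2.11.1, under secondary outcomes, covers the rest of MODE-II: "Maintenance rate of self-exercise program every 3 months during MODE-II (6 and 9 months) will be assessed with phone call assessment". It then adds: "Exercise time using the app will be assessed and compared between the experimental and control groups in MODE-II".

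Section 2.8 (Assessment) says in general terms that primary and secondary outcomes are assessed every three months to month 12. Table 1 schedules participation in self-exercise at each MODE-II time point. Neither says how the quarterly answers combine into nine-month completion.

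**The concern.** The hypothesis and the outcome meant to test it cover different periods. MODE-II lasts nine months, and its primary question looks back three. What happens in the first six months of MODE-II cannot change the primary result.

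The clearest case is a woman who stops when MODE-II begins, does nothing for six months and restarts before month 12. She answers yes at the final call and is counted as having completed nine months. The primary analysis would then compare the arms on activity in the last quarter and report it as nine-month completion. If this is noticed only after the data are in, any redefinition will look post hoc.

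**Working it through.** **The plan's own figure.** Section 2.15 sizes MODE-I at 200 from 60% versus 40%, alpha 0.05 and beta 0.20. With a two-sided test, pooled variance under the null and no continuity correction:

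n per arm = [1.960 × √(2 × 0.5 × 0.5) + 0.842 × √(0.6 × 0.4 + 0.4 × 0.6)]² / (0.6 − 0.4)² = (1.386 + 0.583)² / 0.04 ≈ 97

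That is 194 in total, close to 200. The 160 for MODE-II is 200 × 0.8. No completion rates are given for MODE-II, so no stated figure depends on how its completion is defined.

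**Coverage of the primary question.**
- Start of MODE-II: month 3 (sections 2.7.2.1 and 2.10).
- End of MODE-II: month 12 (section 2.10). Length: 12 − 3 = 9 months.
- Period covered by the month-12 question: months 9 to 12, which is 3 of 9 (33%).
- Not covered: months 3 to 9, which is 6 of 9 (67%).

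**What the two definitions count.** Write Y or N for the answers at the 6-, 9- and 12-month calls, in that order.

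| Pattern | Month-12 answer alone | Yes at all three calls |
|---|---|---|
| YYY | completer | completer |
| NYY | completer | not |
| YNY | completer | not |
| NNY | completer | not |
| any pattern ending in N | not | not |

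The definitions disagree on three patterns, always in the same direction. So the month-12 rate equals the all-three rate plus P(NYY) + P(YNY) + P(NNY), and it can never be the lower of the two.

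**Illustration of the gap within an arm.** Assume the same fraction q answers yes in each quarter. The all-three rate is q³ if quarters are independent and q if they are fully dependent.

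| Assumed q | Independent, q³ | Fully dependent, q | Largest gap in this range |
|---|---|---|---|
| 0.60 | 0.216 | 0.60 | 38 points |
| 0.80 | 0.512 | 0.80 | 29 points |

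**The between-arm difference.** The illustration does not give a direction. With independent quarters, 0.60 versus 0.40 (difference 0.20) becomes 0.216 versus 0.064 (difference 0.152). But 0.80 versus 0.60 (difference 0.20) becomes 0.512 versus 0.216 (difference 0.296).

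**The case against.** The best defence is that the information is already being collected. Calls at 6, 9 and 12 months, each looking back three months, together span the nine months. Section 2.8 and Table 1 schedule them, and a condensed article may leave a combination rule to the full protocol. The first part stands: a reader might infer that the trial cannot measure nine-month completion at all, and that goes too far. The second part does not settle the matter. Section 2.10 names month 12 specifically as the MODE-II primary time point, and section 2.11.1 makes the other two calls a different, secondary outcome. The general schedule in section 2.8 does not override that.

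Several stronger readings are tempting but unsupported:

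- **That app records are kept in both arms and would settle the question.** Both MODE-II arms use an app, and section 2.11.1 compares exercise time on it. The article does not say whether that time is logged automatically or reported by the women. Reminders and badges in the feedback+ app also prompt app use directly, so app time may differ between arms without an equal difference in exercise.
- **That the feedback distorts recall in one arm.** Women know which app they use, and Table 4 shows progress messages in one arm. Those messages concern the day's workout. Nothing in the article shows that they change a yes/no answer about three months, so this is speculation.
- **That a woman who exercised for six months and then stopped is misclassified.** She did not complete nine months, so counting her as a non-completer is correct under either definition.
- **That phone answers would capture exercise done without the app.** The question asks only about exercise using the material provided, which in MODE-II is the app.

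**Conclusion.** The concern holds as a mismatch of period. As written, the MODE-II primary outcome measures reported activity in the last three of nine months, while the hypothesis concerns all nine. The 67% left out follows directly from the text. It rests on MODE-II running from month 3 to month 12, as sections 2.7.2.1 and 2.10 describe.

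The gaps of 38 and 29 points should not be read as an expected overstatement. They rest on assumed quarterly rates and on independent quarters, which is an extreme case for the habits of the same woman. With strongly dependent quarters the gap approaches zero. Nor do they measure bias in the comparison between arms, whose size and direction cannot be derived from the article. The MODE-I outcome has no such problem, because its three-month question matches its three-month period.

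**What to change.** In section 2.10, define MODE-II completion as a positive answer at all three planned calls (6, 9 and 12 months). Keep the month-12 answer alone as a secondary outcome, and align section 2.11.1 so that the 6- and 9-month calls are named as components of the primary outcome. Use the app exercise time already planned for comparison as a supporting analysis. Make it primary only if it is confirmed to be logged automatically in both arms and a threshold is fixed in advance.

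No new calls are needed. The costs are:
- A missed call at any of the three points now affects the primary outcome, so a handling rule must be set in advance.
- The completion rate will be equal to or lower than the month-12 rate.
- The primary outcome has to be amended in a trial that is already enrolling (section 2.2), so this is more than an edit of wording.

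### The primary outcome is named programme completion, but its only stated instrument asks about any use in the past 3 months and no completion criterion is given

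*Protocol article*

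**What the plan says.** Section 2.10 (Primary outcomes) gives the outcome and how it is collected: "The completion rate of the self-exercise program at the completion of MODE-I (3 months) and MODE-II (12 months) will be assessed with phone call assessment". It then prints the one question to be put to participants: "Did you exercise using the app (or booklet) we provided in the past 3 months". No answer options, coding rule or minimum number of sessions follow.

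Section 2.7.1.1 sets the amount of exercise against which completion would be judged: "1 stretching and 1 strengthening exercises for the shoulder, knee, and back (total 6 exercises per day"), with "frequency: 3 times per week; duration: 20 min/day", over 3 months.

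The hypotheses at the end of the Introduction are about completion. For MODE-I they concern 3-month self-exercise, app against booklet. For MODE-II, the feedback+ app "will result in higher completion rates of 9-month self-exercise compared to the feedback- app-delivered exercise program".

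Section 2.15 sizes MODE-I on the same term. It assumes that "the exercise completion rate with 3-month self-exercise using the smartphone app would be 60" per cent, against 40% with the booklet, with alpha 0.05 and beta 0.20, and arrives at 200 participants. It gives neither a source nor a definition for the two rates.

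Two other places touch on adherence. Table 1 has an undefined row for participation in self-exercise. Section 2.11.1 makes exercise time in the app a secondary outcome, for MODE-II only.

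**The concern.** Completing a 3-month programme and having used it at some time in those 3 months are different things. The plan uses the first as the name of the outcome and prints a question about the second. The question asks for no count, frequency or duration, so no completion threshold can be applied to its answer alone.

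This is the primary outcome of both trials. If it is collected as printed, a significant difference would show that more women in one arm used their material at all. It could not be reported as more women completing the programme. A null result would be just as hard to read, because two arms with similar any use can differ widely in how much of the programme was done.

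MODE-II has a further gap. Its hypothesis covers 9 months, but the 12-month call asks about the last 3. A woman who stopped for the first six months of MODE-II and exercised once in the last three could say yes.

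**Working it through.** **1. What one session is worth.** Input: 3 sessions a week (section 2.7.1.1). Over 12 weeks, 3 × 12 = 36; over 13 weeks, 3 × 13 = 39. One session is 1/36 = 2.8% or 1/39 = 2.6% of the prescribed number.

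**2. The MODE-II window.** The hypothesis covers 9 months (Introduction), from month 3 to month 12. The question at 12 months covers 3 of them: 3/9, one third.

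**3. The plan's own sample size.** Inputs (section 2.15): 60% v 40%, alpha 0.05 (taken as two-sided), power 80%, allocation 1:1. Pooled normal formula, with p̄ = 0.5:

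n per arm = [1.960 × √(2 × 0.5 × 0.5) + 0.842 × √(0.6 × 0.4 + 0.4 × 0.6)]² / 0.20²

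= [1.960 × 0.7071 + 0.842 × 0.6928]² / 0.04 = (1.386 + 0.583)² / 0.04 = 96.9, so 97 per arm and 194 in total.

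The stated 200 is within about 3% of this, and 100 per arm gives 81.2% power by the same formula. The arithmetic is sound. What is unsettled is which quantity the 60% and 40% describe.

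**4. Power if the measured quantity is any use.** The documents give no any-use rates, so every pair below is an assumption. Power is the exact probability, summed over both binomial distributions, that the two-sided Pearson chi-square test at 0.05 is significant with 100 per arm.

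| Assumed any use, app v booklet | Difference (points) | Power |
|---|---|---|
| 95% v 90% | 5 | 27% |
| 90% v 80% | 10 | 52% |
| 85% v 70% | 15 | 73% |
| 90% v 75% | 15 | 82% |
| 80% v 60% | 20 | 88% |
| 95% v 80% | 15 | 92% |
| 90% v 70% | 20 | 96% |

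High rates do not by themselves cost power. With a 20-point difference, power is higher at 90% v 70% than at 60% v 40%, because the variance is smaller. Power falls only if the difference narrows enough.

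**5. When it would narrow.** Take 60% and 40% as true completion, let every completer say yes, and let a share q of non-completers say yes because they exercised at least once. The observed rate is p + (1 − p)q. With the same q in both arms the difference is 0.20 × (1 − q), so it must shrink. Power is by the formula in step 3.

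| q (assumed) | Observed rates | Power at 100 per arm | Total N for 80% power |
|---|---|---|---|
| 0 | 60% v 40% | 81% | 194 |
| 0.25 | 70% v 55% | 59% | 326 |
| 0.50 | 80% v 70% | 37% | 588 |
| 0.75 | 90% v 85% | 19% | 1372 |

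The result depends on q being equal. If q is 1/2 in the app arm and 1/3 in the booklet arm, the rates are 0.60 + 0.40/2 = 80% and 0.40 + 0.60/3 = 60%. The difference stays at 20 points and power is 88% (step 4). The documents do not say which case applies.

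**The case against.** The strongest reply is that this is a condensed article. It prints a question but no scoring rule, and a call script or full protocol may hold follow-up items and a threshold. This stands against one tempting reading, that the plan scores a single session as completion. No such rule is written. That one session permits a yes follows from the wording and the absence of a criterion. The reply does not remove the point, because the objection is to the question as stated. A threshold kept elsewhere could not be applied to an any-use answer. If the call asks more than is printed, section 2.10 misdescribes the primary outcome and should say so.

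Second, the 60% and 40% may have been set with this very question in mind. A reader might infer that the trial is sized on a different quantity from the one it measures. Section 2.15 does not settle that. If the rates were meant as any use, the sample size fits the instrument and the fault lies in calling the outcome completion. What can be said is that they are not shown to refer to any use.

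Third, a reader might expect nearly every volunteer to report some use, so that both arms sit near the ceiling and power collapses. No figure in the article supports this. Step 4 shows that power could also exceed 80%.

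Fourth, app exercise time gives MODE-II a graded adherence measure. That is true, but it is secondary, and it is listed for MODE-II only. It cannot define the MODE-I primary outcome, where the booklet arm has no app record.

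**Conclusion.** The point holds as a fault in the measurement rule for the primary outcome. The stated question captures any use, the outcome is called completion, and nothing in the article connects the two. One of about 36 to 39 prescribed sessions is enough for a truthful yes, and for MODE-II the question reaches only a third of the hypothesised period. These statements rest on the printed wording and the prescribed frequency. The one inference is that the question is answered yes or no, which its form implies.

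The consequence that can be asserted firmly is for interpretation: the primary result, whichever way it falls, could not be reported as a result on completion. A loss of power cannot be asserted. Across the assumed any-use rates, power at 100 per arm runs from 27% to 96%. The fall to between 59% and 19% in the dilution model depends on an equal q in both arms, for which the documents give no figure. It should be fixed before the primary outcome is used.

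**What to change.** - **Question.** In the same phone call, worded alike in both arms, ask in how many weeks of the past 3 months the programme was done and on how many days in a usual week.
- **Definition.** In section 2.10, define completion as a fixed share of the prescribed sessions. The investigators should choose the share and record it before any 3-month data are seen.
- **MODE-II.** Combine the 6-, 9- and 12-month calls so that the outcome covers all 9 months of the hypothesis.
- **Sample size.** State in section 2.15 that 60% and 40% refer to this definition. If they do not, restate the assumption and the power.
- **Any use.** Keep the present question as a secondary outcome under that name.

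The cost is one reworded phone item, one definition and one sentence in the sample size section. Counts recalled over 3 months carry some error, and observed completion may be lower than the share who would say yes to the present question. Section 2.2 reports that recruitment has begun. If any 3-month calls have already been made with the printed wording, this should be documented, because session counts for the booklet arm could not be reliably recovered afterwards.
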